**Implementation evaluation**																									
	Intention to adopt: ACCEPT-VFCC^l^		Therapists		✓		✓		✓		✓		✓		✓		✓		✓			✓		✓	
	**Fidelity to FCT^m^ practices**																								
		FCT fidelity checklist	Therapists		✓		✓		✓		✓		✓		✓		✓		✓			✓		✓	
		PRIME-SP^n^	Therapists		✓		✓		✓		✓		✓		✓		✓		✓			✓		✓	
	**Documentation of TIPS coadaptation**																								
		Organizational readiness for eHealth questionnaire	Managers		✓																				
		Group discussion recordings	Leadership team				✓																		
	**Influencing factors**																								
		Monthly therapists’ meetings recordings	Therapists										✓		✓		✓		✓						
		Virtual community of practice discussion threads	Therapists										✓		✓		✓		✓						
**Effectiveness evaluation**																									
	Service wait times: time from service eligibility to first scheduled appointment		Managers		✓																	✓			
	Perceptions of service quality: MPOC-20^o^		Parents		✓																	✓			
	Changes in service delivery: semistructured interviews		Managers, therapist champions, therapists, and parents																			✓			
	**Costs**																								
		Organizational costs	Managers																			✓			
		Family costs	Parents		✓																	✓			
		Implementation cost (cost journal)	Research team				✓		✓		✓		✓		✓		✓		✓						

^a^TIPS: training intervention and program of support.

^b^T–3: 3 months before implementation.

^c^T–2: 2 months before implementation.

^d^T–1: 1 month before implementation.

^e^T0: implementation initiation.

^f^T1: 1 month after implementation + end of training intervention.

^g^T2: 4 months after implementation.

^h^T3: 8 months after implementation.

^i^T4: 12 months after implementation + end of support program.

^j^T5: 15 months after implementation.

^k^T6: 18 months after implementation+6 months after end of implementation.

^l^ACCEPT-VFCC: Assessment of Competencies and Contributors to Enhance Practice Transition to Virtual Family Centered Care Survey.

^m^FCT: family-centered telehealth.

^n^PRIME-SP: Pediatric Rehabilitation Intervention Measure of Engagement-Service Provider version.

^o^MPOC-20: Measure of Processes of Care-20.

### Implementation Evaluation

#### Overview

The implementation evaluation will primarily seek *to assess therapists’ intention to, and adoption of FCT, and their fidelity to FCT practices* (ie, objective 1). An interrupted time series was selected to assess primary implementation outcomes as recommended for research in real-world settings [78,79]. Unlike other design types that rely on randomization (eg, stepped wedge), this design allows for site leadership teams to be included in the discussion about the timing of the initiation of the intervention [80]. An interrupted time series consists of observing the same dependent variables over time with a break in the series of observations corresponding to the introduction of an intervention. If the intervention is effective, a change in the series’ pre- and postintervention averages will be observed [79]. TIPS will be implemented in all sites in a specified jurisdiction during the same month and sequentially introduced across all jurisdictions, 2 months apart. Implementation data will be collected at least 3 times during each study period [81]: before (T–3 to T–1), during (T0 to T3), and after the implementation of TIPS (T4 to T6). The additional data collection time point at 1 month following the TIPS implementation will allow documentation of the short-term impact of the *training intervention* portion of TIPS (ie, the self-paced modules and webinar). Statistical analysis models will account for the inequivalent time intervals across study periods [75].

#### Data Collection

The *therapist’s implementation questionnaire*, completed electronically by therapists at multiple time points (ie, T–3 to T6), will include questionnaires addressing the *primary objectives* and will comprise the measures discussed next.

To compare changes in therapists’ intention to, and adoption of, FCT (ie, objective 1), the *Assessment of Competencies and Contributors to Enhance Practice Transition to Virtual Family Centered Care survey* will be used. This measure, based on the validated Theoretical Domain Framework Questionnaire template [81-83], examines 8 constructs across 41 items and considers factors, including knowledge and skills, social or professional role identity, beliefs in capacity-building attitudes, therapists’ intention to adopt a virtual practice based on FCT, and environmental, patient-targeted, and other factors perceived to affect FCT implementation. Therapist participants will be asked to rate their responses to 36 specific statements associated with each theoretical domain framework domain using a 7-point Likert scale (1=strongly disagree to 7=strongly agree). A total of 4 open-ended or multiple-choice questions related to identification of facilitators and barriers and training preferences round out the instrument. Furthermore, the number of FCT sessions conducted in the proceeding months will document the actual adoption of FCT by therapists. Upon the initial completion (ie, at T–3), participants will be asked to respond to questions associated with sociodemographic characteristics (eg, professional education and work experience) and their previous telehealth experience, including prior training and use. This section will not be repeated at subsequent data collection time points (ie, T–2 to T6).

To monitor therapist fidelity to FCT practices (ie, objective 1b), the *FCT fidelity self-perceived checklist* and *Pediatric Rehabilitation Intervention Measure of Engagement-Service Provider version (PRIME-SP)* will be used. The *FCT fidelity self-perceived checklist*, a 4-item instrument, developed and pilot tested in a previous study [84], will measure therapists’ perceptions of the perceived quality of 3 interventional behaviors associated with the FCT clinical intervention (ie, goal focused, active parent partnerships, and evidence of supportive and trusting parent-professional relationships) based on their last telehealth session. Each behavior, comprising 4 criteria, is scored on a 5-point Likert scale (0=behavior not implemented when it should have been to 4=all the identified behaviors were implemented when appropriate and within context). The fourth item assesses the representability of the chosen session to a typical parent-therapist interaction. The *PRIME-SP* will be used to measure therapists’ views on how engagement practices were implemented with clients during their last telehealth session and the clients’ responses [85]. It consists of an overall rating, as well as separate ratings of affective, cognitive, and behavioral aspects of a client’s engagement state, based on a 4-point descriptive scale (disengaged to extremely engaged). Face, content, and construct validity of the PRIME-SP have been established [85].

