## Introduction

### Background

Timely access to family-centered services for children with disabilities and their families is crucial for supporting their development and well-being [1-3]. Currently, many children face long wait times (ie, up to 2 years) as well as organizational, geographic, or cultural barriers to services [4-6]. Lack of service access can lead to negative developmental, health, and social consequences for children and their families [7-10]. The COVID-19 pandemic further exacerbated these issues, as rehabilitation support for children was significantly reduced [11], increasing parental mental health burden (eg, stress and depression) [7-10]. To minimize the negative impacts of these service disruptions, therapists shifted to telehealth service delivery [7,9,12,13].

Telehealth is defined as any asynchronous or real-time clinical intervention provided remotely by clinicians (in this case, therapists) to patients or caregivers [14-16]. Telehealth is an important alternative for families living in underserved or remote areas [14,17-21]. However, some families in well-served urban locations also prefer the convenience of telehealth over in-person visits for reasons such as decreased travel time and schedule flexibility [15,16]. Before the COVID-19 pandemic, a systematic review of randomized controlled trials of pediatric rehabilitation delivered via telehealth supported the efficacy of rehabilitation provided via telehealth for diverse populations and a wide range of effects, including improved service access, child outcomes (eg, behavior), and family satisfaction [22]. Telehealth interventions have yielded promising results [23,24], and the acceptability [17,25-28] of telehealth has been previously established, further supporting its integration into comprehensive family-centered services [17,27,29,30].

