Family-centered telerehabilitation (FCT) is defined as pediatric rehabilitation that uses family-centered care practices while working with families remotely. Family-centered care is recognized as the best practice approach in pediatric rehabilitation [44]. Described as a partnership approach, family-centered care is based on the belief that the child’s well-being and care needs are best supported within the family context through effective family-provider collaborations [45]. A central family-centered care tenet is the assumption that the processes of care delivery are as important to child and family outcomes as the specific characteristics of the clinical intervention delivered [45]. Family-centered care is characterized by practices that promote clinical flexibility; respect and dignity for families’ perspectives, knowledge, strengths, and characteristics; effective information sharing (general and specific), partnership, and collaboration among parties to support decision-making; and coordinated and comprehensive care delivery [30]. Furthermore, family-centered care occurs in therapeutic environments that optimize the development of family-provider partnerships [46-49], in which parents are active participants in collaborative goal-setting therapy [50,51], planning, implementation, and evaluation [44,46,52,53] and where activities are integrated within daily routines and contexts such as home and community [54].

Telehealth offers additional opportunities to enhance family-centered care practices [30,55] as it provides convenient and flexible ways to partner with families, respecting individual family composition, characteristics, and constraints (eg, geographical, temporal, and financial) [21]. Furthermore, it allows real-time knowledge acquisition and information sharing about the child within their contexts and supports family decision-making and parents’ psychosocial well-being such as decreased anxiety, stress, and depression [21]. Finally, telehealth has been recognized as an important addition to comprehensive care coordination and service delivery [56].

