**Figure 1 figure1:**

Training intervention and program of support description. FCT: family-centered telerehabilitation; KB: knowledge broker; vCoP: virtual community of practice.

The TIPS self-paced learning modules are informed by contemporary family-centered care frameworks and the family-oriented service continuum [30]. More specifically, they will address FCT core components and provide practice examples. Modules will address the following topics, as they apply to telehealth: (1) overview of family-centered care premises and principles (eg, information provision; respectful, supportive, and comprehensive care; and enabling partnerships) [63,64], (2) parent-professional collaborative partnerships (eg, goal cocreation, parent and child engagement, and role negotiation) and helpful FCT instruments and strategies [65], (3) coaching in the FCT context (eg, various approaches and strategies) [52,66], and (4) factors influencing service delivery model choice (ie, face-to-face or telehealth) [12]. As per best practice [16] and using education course creation software, several members of the study team will codevelop multimedia content (eg, videos and presentations) for the asynchronous training in consultation with pediatric clinicians and other experts (eg, parent partners, national organizational partners, inclusion and diversity experts, and knowledge keepers). We will upload the curriculum to a password-protected web-based platform for which a unique username and password will be required. Knowledge acquisition, based on specified learning objectives and key messages targeted in each training module, will be assessed through short quizzes. Completion of the asynchronous modular training and knowledge assessment will be recommended before undertaking the synchronous webinar.

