A 6-hour synchronous webinar component will also be delivered to participants by members of the research team and 3 knowledge brokers. The webinars will engage therapists in discussions using case studies and interactive activities (eg, role play, vignettes, and simulations) to build their critical thinking on how to implement these practices in their context and with the families they serve. The webinar content will be adapted for each site in consultation with the local leadership team (ie, a site manager, a therapist champion, and a parent or patient partner). This coadaptation phase will ensure that activities and practice examples are tailored to individual site contexts and processes (eg, engagement practices, site clinical goal-setting processes, and service coordination as per team procedures) and that webinars are learner-centered and clinically relevant. Therapists will be encouraged to consider various asynchronous and real-time technologies, including email, telephone, web-based platforms, and videoconferencing systems that best respond to families’ needs and preferences and are approved by their organizations. The research team will refrain from recommending specific technologies. There will be no prescribed frequency or duration for the FCT interventions; rather, therapist participants will work with families according to their goals and preferences, and site-specific organizational policies.

Finally, a program of support will be offered for the remaining year via monthly videoconference mentoring meetings and access to the virtual community of practice, which will be housed on the password-protected web-based platform. Monthly meetings will focus on sharing site-specific successes and challenges, proposing solutions and reporting results, as well as sharing practical evidence-informed resources. The evidence-informed virtual community of practice, facilitated by the 3 national knowledge brokers, will be used to canvas for solutions to address challenges at a national level; share successes; discuss specific cases for guidance, feedback, and input; and share useful tips, tricks, and resources [43,59,67-71].

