#### Data Analysis

To evaluate implementation (ie, objective 1), longitudinal mixed modeling accounting for and considering potential methodological issues associated with an interrupted time series analysis (eg, autocorrelation and time-varying confounders) will be used to analyze implementation indicators (ie*,* Assessment of Competencies and Contributors to Enhance Practice Transition to Virtual Family Centered Care survey, therapists’ self-reported FCT frequency, FCT fidelity self-perceived checklist, and PRIME-SP). Changes will be documented in the short term (ie, 1 month after TIPS introduction) and in the long term (ie, at the end of TIPS, 12 months after its introduction). Models will be covariate-adjusted to reduce potential confounding bias, including the therapists’ characteristics (eg, gender and years of experience) and site characteristics (eg, service provided, geography, and general patient characteristics), to estimate associations of key explanatory variables alongside TIPS. Secondary analyses will explore the heterogeneity in changes of outcome measures across genders, sites, therapists, and health jurisdiction levels.

*Secondary implementation objectives* will be evaluated using a multimethod approach.

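### Actual adoption rests on a self-reported count of FCT sessions, and TIPS teaches what counts as FCT, so the count could shift at the interruption without a change in practice

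*Protocol article*

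**What the plan says.** Under Implementation Evaluation, Data Collection, the protocol article states that "the number of FCT sessions conducted in the proceeding months will document the actual adoption of FCT by therapists". The Data Analysis section lists this indicator as "therapists’ self-reported FCT frequency", so the source is the therapist. No service log or billing record is named.

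The other therapist measures do not record how much FCT is delivered. The ACCEPT-VFCC survey is introduced for intention and adoption, but its described content is intention, determinants, barriers and training preferences. The fidelity checklist and the PRIME-SP each rate a single session; for the PRIME-SP the wording is "during their last telehealth session".

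The Background section defines telehealth as "any asynchronous or real-time clinical intervention provided remotely by clinicians" and FCT as "pediatric rehabilitation that uses family-centered care practices while working with families remotely". On TIPS, the Intervention section says of the learning modules that "they will address FCT core components and provide practice examples". It says of the webinar: "Therapists will be encouraged to consider various asynchronous and real-time technologies, including email, telephone, web-based platforms, and videoconferencing systems".

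**The concern.** An interrupted time series needs the outcome to mean the same thing before and after the break. The Implementation Evaluation overview says as much: it describes observing the same dependent variables over time and reads a difference between the averages before and after as the effect.

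Here the therapist decides which contacts are FCT, and the intervention teaches how to decide. A therapist who learns that a coaching call or an email exchange can be FCT may begin to count contacts that were already taking place. One who learns a stricter idea of family-centered practice may stop counting sessions that were counted before. Either change would coincide with TIPS.

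The research question asks whether TIPS enhances adoption, and this count is the only behavioural evidence on it. The article expects only minimal change at 1 month and modest change later, so a small artefact could be as large as the expected signal. The adoption result also has later uses: interviewees are chosen partly by high or low adoption, and incremental cost ratios divide by change in the primary implementation outcomes.

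**Working it through.** **1. The passages side by side**

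- Unit counted: FCT sessions, reported by the therapist (Data Collection; Data Analysis).
- Condition for a contact to qualify: remote, and using family-centered practices (Background). The second part is a judgement.
- What TIPS changes: it teaches the core components of FCT with examples, and it names email and telephone among the modes to consider (Intervention).
- When: training runs from T0 to T1, which is the interruption.

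It follows that a shift in classification at the interruption is possible. It does not follow that one occurs, or in which direction.

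**2. Do other design features remove the risk?**

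- Staggered rollout: no. Each region receives the teaching at its own start, so the shift would move with the intervention.
- Covariates: no. The adjustment covers therapist and site characteristics, not how contacts are classified.
- Is there existing remote work to reclassify? Plausibly. The Background section reports that 70.1% of a surveyed subsample had adopted telehealth by May 2020.

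**3. The plan's own figure**

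The Sample Size section claims more than 80% power for d ≥ 0.5 with 300 therapists, 10 time points, autocorrelation below 0.3 and a Šidák correction. Check: generalised least squares segmented regression at months −3, −2, −1, 0, 1, 4, 8, 12, 15 and 18, with first-order autocorrelation 0.3 between successive visits and unit SD. The number of outcomes k is not stated and is taken as 1 to 8.

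- α = 1 − 0.95^(1/k)
- Power = Φ(0.5/SE − z(1−α/2))
- With the break at T1 and a slope change, SE = 0.079. For k = 4, α = 0.0127 and power = 0.9999.
- With the break at T0 or T1, with or without a slope change, and k = 1, 2, 4 or 8, power is 0.998 to 1.000.

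The claim holds as a lower bound and is not in dispute. The same SE gives the level change detectable with 80% power, SE × (z(1−α/2) + 0.842):

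- k = 1: 0.079 × (1.960 + 0.842) = 0.22
- k = 8: 0.079 × (2.727 + 0.842) = 0.28

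Site clustering is left out because the article gives no intraclass correlation, so the true SE is likely to be larger.

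**4. Illustration on assumed inputs**

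All inputs here are assumptions. Actual remote work is unchanged: v video sessions and e telephone or email contacts per therapist per month, each 2, 4 or 8. A share r0 of the latter is counted as FCT before training and r1 after. The SD is set equal to the mean count before training.

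Count before = v + e·r0; count after = v + e·r1; d = (after − before)/before.

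| v | e | r0 | r1 | before | after | ratio | d |
|---|---|---|---|---|---|---|---|
| 8 | 2 | 0 | 0.25 | 8 | 8.5 | 1.06 | 0.06 |
| 4 | 8 | 0 | 0.25 | 4 | 6 | 1.50 | 0.50 |
| 2 | 8 | 0 | 0.50 | 2 | 6 | 3.00 | 2.00 |
| 8 | 2 | 0.50 | 0.25 | 9 | 8.5 | 0.94 | −0.06 |
| 2 | 8 | 0.50 | 0.25 | 6 | 4 | 0.67 | −0.33 |

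First and third rows: the smallest and largest rise in the grid. Last two rows: the smallest and largest fall. With v = 4, e = 8 and SD = 4, newly counting 0.22 × 4/8 = 11% to 0.28 × 4/8 = 14% of the other contacts would equal the detectable effect. The range is too wide to serve as an estimate. It shows only that a shift large enough to matter cannot be ruled out.

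**The case against.** **The questionnaire is not shown.** It may print a definition of an FCT session, and a journal article commonly leaves item wording to the form. This stands, and it limits the point to a risk in the outcome as described. A reader might infer that untrained therapists do use their own idea of FCT and that the measuring rule does change; no passage says so. A printed definition would remove the problem, however, only if it were identical from T–3 onward and needed no judgement about family-centeredness.

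**The definitions are consistent.** A reader might infer that adoption and fidelity use conflicting units. They do not. FCT is the family-centered form of telehealth, and rating fidelity only in sessions already judged family-centered would be circular. A reader might also take the telehealth definition to name email and telephone. It does not; the Intervention section names them, as technologies to consider.

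**New FCT by email or telephone is real adoption.** This stands. The difficulty is that one FCT count cannot tell new work from newly labelled work.

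**Therapists already linked telephone with telehealth.** In the survey cited in the Background section they asked for training in communicating by telephone and internet. This weakens the assumption that no such contacts were counted before training.

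**The shape over time helps.** A definition learned in the training month should appear as an early step, while growth from T2 to T6 is harder to explain that way. This stands in part: the early step is itself reported as the short-term effect, and a lasting shift in level would also enter the 12-month change. Recorded meetings, discussion threads and interviews could reveal relabelling but would not measure it.

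**The count is not the headline.** The stated primary objectives are intention and fidelity, and the limitations section concedes self-report and study-specific measures. But the Implementation Evaluation overview and Data Analysis sections include adoption in objective 1, and the limitation does not mention a shift in meaning at the interruption.

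**Conclusion.** The point holds as a risk of response shift, and it is a cheap improvement rather than an error in the plan. The only described measure of actual adoption depends on a judgement that the intervention teaches, so a change in the FCT count at the interruption, taken alone, does not show a change in practice.

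The direction is unknown, and the size cannot be computed from the documents. The illustrative range (a count ratio of 0.67 to 3.00) rests wholly on assumed contact numbers, counted shares and SD. The conclusion also assumes that the questionnaire does not already fix the unit without a judgement about family-centeredness.

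A reader might go further and conclude that real-time remote sessions should become the adoption indicator. The documents do not support that. It would measure telehealth volume rather than FCT adoption, and it would drop the asynchronous work that the article includes in telehealth and encourages in training.

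**What to change.** At every time point from T–3 to T6:

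- Keep the FCT session count.
- Add counts that need no judgement about family-centeredness, under one printed definition that never changes: video sessions, telephone sessions, asynchronous clinical contacts and in-person sessions.
- Report all remote contacts by modality, as counts and as a share of all contacts, beside the FCT count.
- State in advance that a rise in the FCT count will be attributed to changed practice only if the modality counts or the fidelity checklist support it.

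The definitions of telehealth and FCT and the session rated for fidelity can stay as they are. The items must be in place before T–3, because a baseline collected without them cannot be rebuilt from the questionnaire.

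The cost is four short numeric items in an existing electronic questionnaire. The drawback is slightly more response burden at ten time points, in a study whose limitations section already warns of missing data.
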